## Abstract

**Background::**

Hypertension, together with poorly controlled blood pressure (BP) are known risk factors for kidney disease and progression to kidney failure as well as increased cardiovascular (CV) morbidity and mortality. Several studies in patients without kidney disease have demonstrated the efficacy of home BP telemonitoring (HBPT) for BP control.

**Objective::**

The primary aim of this study is to assess the mean difference in systolic BP (SBP) at 12 months, from baseline in remote dwelling patients with hypertension and chronic kidney disease (CKD) in Northern Alberta, Canada, comparing HBPT + usual care versus HBPT + a case manager. Other secondary objectives, including cost-effectiveness and acceptability of HBPT as well as occurrence of adverse events will also be assessed.

**Methods:**

**Design::**

This study is designed as a pragmatic randomized controlled trial (RCT) of HBPT plus clinical case management compared to HBPT with usual care.

**Setting::**

Peace River region in Northern Alberta Region, Canada.

**Patients::**

Primary care patients with CKD and hypertension.

**Measurements::**

Eligible patients will be randomized 1:1 to HBPT + BP case management versus HBPT + usual care. In the intervention arm, BP will be measured 4 times daily for 1 week, with medications titrated up or down by the study case manager until guideline targets (systolic BP [SBP]: <130 mmHg) are achieved. Once BP is controlled, (ie, to guideline-concordant targets), this 1-week protocol will be repeated every 3 months for 1 year. Patients in the control arm will also follow the same BP measurement protocol; however, there will be no interactions with the case manager; they will share their BP readings with their primary care physicians or nurse practitioners at scheduled visits.

**Limitations::**

Potential limitations of this study include the relatively short duration of follow-up, possible technological pitfalls, and need for patients to own a smartphone and have access to the internet to participate.

**Conclusions::**

As this study will focus on a high-risk population that has been characterized by a large care gap, it will generate important evidence that would allow targeted and effective population-level strategies to be implemented to improve health outcomes for high-risk hypertensive CKD patients in Canada’s remote communities.

**Trial Registration::**

www.clinicaltrials.gov (NCT number: NCT04098354)

## Introduction

Poorly controlled blood pressure (BP) is a risk factor for rapid progression of chronic kidney disease (CKD) to kidney failure and is also associated with cardiovascular (CV) morbidity and mortality.^1-4^ Poorly controlled BP is common and often associated with a higher rate of adverse clinical outcomes among remote/rural dwellers due to limited access to and lower quality of chronic disease care.^3,5^ Recent data have demonstrated that remote dwellers with CKD have less access to specialist care, receive poorer clinical care in all aspects of the care process, and exhibit worse clinical outcomes compared to their counterparts living in urban centers.^1,6-9^ Notably, among remote dwellers with CKD, a lack of BP control is the most important identified element of evidence-based care that is amenable to intervention.^1,9^

Recent guidelines by Kidney Disease Improving Global Outcomes (KDIGO) recommend that systolic blood pressure (SBP) be lowered to <120 mmHg in all patients (**
*level 2B—*
**if tolerated, because of potential harms and lack of evidence in special groups) but to aim for <130 mmHg or even higher if a lower target is not tolerated.^
10
^ Guidelines from Hypertension Canada, however, still recommend ≤130 mmHg or ≤ 120 mmHg in patients with diabetes or CKD and <140 mmHg in all other patients.^
11
^ BP is the most important prognostic factor for CKD clinical outcomes;^
12
^ however, among patients with CKD (Stages 3 and 4), only a fraction meet the recommended BP targets using existing care approaches.^4,12-15^ Contemporary BP management guidelines recommend shifting from office-based BP measurement to home/ambulatory readings because the latter are more prognostically accurate: well-conducted randomized controlled trials (RCTs) provide strong evidence of the benefits of home BP monitoring compared to conventional office measures.^2,16-21^

Several studies have demonstrated the feasibility and accuracy of home BP telemonitoring (HBPT) and increased patient satisfaction compared to the usual care among those with some chronic conditions.,^15,22^ In 1 study, when compared to usual care, the adjusted mean SBP differences with HBPT was −4·7 mm Hg (–7·0 to −2·4; *P* < .0001) and when HBPT was combined with additional care (eg, counseling, education, behavioral management, etc) the mean reduction in SBP and DBP was of a larger magnitude, suggesting that HBPT can be more efficacious when proactive additional support is provided.^
23
^ Findings from recent reviews and meta-analyses also show the positive impact of telemonitoring on patient outcomes for those with chronic conditions such as diabetes, asthma, and heart failure.^24-27^ One systematic review and meta-analysis on the effects of HBPT on blood pressure and kidney function in CKD patients reported significant reduction of SBP (-8.8 mmHg; [95% CI: -16.2, -1.4]; *P* = .02) and DBP (-2.4 mmHg; [-3.8, -1.0]; *P* < .001), and significant improvement in estimated glomerular filtration rate (5.35 mL/min/1.73 m^2^; [2.49, 8.21]; *P* < 0.001).^
28
^ Canadians living in remote communities continue to experience various challenges in accessing healthcare; lack of access to healthcare services and treatments in such settings is often compounded by geographical isolation from mainstream health services. Hence, the use of HBPT technologies could prove to be advantageous for improving control of hypertension and reducing associated target organ damage in populations in remote regions. However, the clinical efficacy, safety, acceptability, and cost-effectiveness of HBPT among CKD patients living in remote/rural communities with limited access to care is unknown.

Therefore, the primary aim of this study is to assess the mean difference in SBP at 12 months, from baseline in remote communities in Northern Alberta through a pragmatic RCT, comparing HBPT + usual care versus HBPT + a case manager.

## Methods

### Study Objectives

The primary aim of this study is to assess the mean difference in SBP at 12 months, from baseline in remote communities in Northern Alberta through a pragmatic RCT, comparing HBPT + usual care versus HBPT + a case manager. Secondary aims of the study will include:

Proportion of patients who maintained home SBP within guideline target (<130 mmHg)^10,11^ from baseline to the end of the study.Proportion of patients who remained within guideline target SBP (<130 mmHg),^10,11^ throughout the study.The user acceptability of HBPT for BP control, using a qualitative approach.The cost-effectiveness and cost utility of HBPT combined with a protocol-based case management approach among remote-dwellers with CKD compared to the usual care.5.Proportion of adverse events, eg, syncope, hypotension requiring assistance or medical attention, worsening of kidney function (2x serum creatinine or 50% decline in estimated glomerular filtration rate [eGFR]), and/or electrolyte abnormalities [hyperkalemia ≥ 6.5 mmol/L], in each arm of the study.

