### Outcomes

The primary outcome will be the mean difference (MD) in home SBP at 12 months, from baseline values. Secondary outcomes will include (1) proportion of patients with SBP within guideline target at end of the study, from baseline; (2) Proportion of patients who remained within target SBP throughout the study; (3) user acceptability of HBPT for BP control; (4) cost-effectiveness and cost utility of HBPT combined with a protocol-based case management approach, and (5) adverse events reported.

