### Sample Size Estimation

The sample size calculation for this trial is based on the data from HBPT plus pharmacist management trial on the hypertension population.^
22
^ Adequate power will be used to detect a clinically important absolute difference in mean SBP of 10 mmHg between the intervention arm and the control arm (usual care). Using a 2-sample t-test, alpha of 0.05 and power of 0.80, and assuming a common standard deviation of 19 mmHg, the required sample size will be ~58 patients per arm, or 116 in total. Accounting for ~20% attrition over 1 year, we will recruit 73 patients per arm, for a total of 146 patients. This sample size is also powered to detect a difference of 20% in the proportion of patients who maintain the guideline target of SBP (alpha 0.05, power 80%, and assuming event occurs 50% in the control group).^
22
^

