### Plan for Data and Statistical Analysis

Baseline statistics and the outcome variables will be described using counts and proportions, mean (SD) or median (interquartile range) as appropriate. All analyses will follow the intention-to-treat principle. We will estimate the effect size as the mean difference of SBP between groups at 12 months using a mixed linear-regression model include fixed-effects term for time point (6 months and 12 months), intervention, their interaction, and a random-effect term for participants. For the dichotomous outcomes (patients who maintained the SBP guideline and adverse outcomes), we will use Poisson regression with robust error variance to test the effect of the intervention.^
50
^ Continuous outcomes without repeated measurement will be examined using linear regression. We will adjust for eGFR for all the analyses. All estimated effect sizes will be reported along with 95% confidence intervals, and P<0.05 was considered statistically significant. We will analyze the data using Stata/MP 17.0 software (www.stata.com).

We will use multiple imputation method for missing data. Imputation of missing SBP values will only apply in instances when participants do not have any blood pressure recordings for the entire week. We will impute the missing SBP within each randomized group using age and sex separately at 6 months and 12 months. Estimate from each imputed data set will be combined using Rubin’s method.^
51
^ No interim analyses are planned due to the short duration of the study. However, for subgroup analysis, we will use the model from the analysis for primary analysis to explore the relationship between intervention and eGFR groups, age groups, the presence of diabetes, and so on.

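### Secondary outcome 1 (SBP at target) has two incompatible definitions, and on the Objectives wording a patient at or above 130 mmHg at entry can never count as a success

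*Protocol article*

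**What the plan says.** Four sections of the protocol article describe target attainment.

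- **Study Objectives**, aim 1: "Proportion of patients who maintained home SBP within guideline target (<130 mmHg)^10,11^ from baseline to the end of the study". Aim 2: "Proportion of patients who remained within guideline target SBP (<130 mmHg),^10,11^ throughout the study".
- **Outcomes**, outcome 1: "proportion of patients with SBP within guideline target at end of the study, from baseline". Outcome 2: "Proportion of patients who remained within target SBP throughout the study".
- **Sample Size Estimation**: "This sample size is also powered to detect a difference of 20% in the proportion of patients who maintain the guideline target of SBP", with "alpha 0.05, power 80%, and assuming event occurs 50% in the control group".
- **Plan for Data and Statistical Analysis**: "For the dichotomous outcomes (patients who maintained the SBP guideline and adverse outcomes), we will use Poisson regression with robust error variance".

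Three other parts bear on how these read. The eligibility list (Study population) requires treated hypertension but sets no SBP threshold. The Abstract (Measurements) has the case manager adjust medication until SBP is below 130 mmHg. Under Intervention arm, the 7-day series is repeated monthly until SBP is in range and quarterly after that; the control arm follows the same measurement protocol.

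**The concern.** The same numbered outcome is a sustained state starting at baseline in one section and a status at one time point in another. The sections that power and analyse it use a third, shorter label that fits either.

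The choice matters because of who is enrolled and what the case manager does. Patients above target may enter, and the intervention is built to bring them to target. If control must hold from baseline, every such patient is a failure on the day of randomisation, however well treatment works. The outcome then records only whether patients who were controlled at entry stay controlled, and most of what the case manager is there to achieve goes uncounted. This is also the only secondary outcome for which the article claims power.

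**Working it through.** **1. The definitions applied to one patient.** Home SBP is 150 mmHg at entry and 125 mmHg at 12 months.

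| Section | Requirement | Result |
|---|---|---|
| Objectives, aim 1 | below 130 from baseline to end | failure |
| Outcomes, outcome 1 | below 130 at end | success |
| Objectives aim 2, Outcomes outcome 2 | below 130 throughout | failure if baseline counts; otherwise depends on which later series count |
| Sample size; analysis | target maintained | not determined |

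Within the Objectives list, aims 1 and 2 are nearly the same quantity. Within the Outcomes section they are distinct.

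**2. The ceiling.** Let q be the share below 130 mmHg at entry and r the share of those who stay below. On the Objectives wording, success = q × r. Since r cannot exceed 1, success cannot exceed q.

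- Control at 50% needs q of at least 0.50.
- Intervention at 70% (50% plus an absolute 20 points) needs q of at least 0.70.
- If the 20% were relative, the intervention rate would be 0.50 × 1.20 = 60%, and q would need to be at least 0.60.

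The documents give no value for q. The Introduction says, without a figure, that just a fraction of patients with stage 3 and 4 CKD reach recommended targets under existing care.

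**3. The plan's own figures.** The primary calculation reproduces. With difference 10, SD 19, two-sided alpha 0.05 and power 0.80, a t-test needs 57.6, so 58 per arm, and 58 / 0.80 = 72.5, so 73. The binary claim does not. Using

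power = Φ{ [Δ√n − 1.96 √(2p̄(1−p̄))] / √(p₁(1−p₁) + p₂(1−p₂)) }

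with 0.50 versus 0.70 (Δ = 0.20, p̄ = 0.60):

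- n = 58: (1.523 − 1.358) / 0.678 = 0.244, power 0.596.
- n = 73: (1.709 − 1.358) / 0.678 = 0.517, power 0.698.

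That shortfall exists whichever definition is used and is a separate matter. It is shown here as the reference for step 4.

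**4. Dilution on the Objectives wording.** Assume, for illustration, that 50% versus 70% applies to retention among those at target at entry, and vary q.

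| q (assumed) | Control vs intervention | Power, 58 per arm | Power, 73 per arm |
|---|---|---|---|
| 0.3 | 15% vs 21% | 0.131 | 0.154 |
| 0.5 | 25% vs 35% | 0.215 | 0.259 |
| 0.7 | 35% vs 49% | 0.331 | 0.402 |
| 1.0 | 50% vs 70% | 0.596 | 0.698 |

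At q = 0.5 the 20-point difference shrinks to 0.5 × 20 = 10 points.

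**The case against.** The best defence is that the word "maintain" is used loosely and that attainment at 12 months was always meant. The Outcomes section says so, and the 50% versus 70% assumption fits attainment better than unbroken control from baseline. Only aim 1 in the Objectives ties control explicitly to baseline; the sample-size and analysis sections do not. This is a fair guess at intent and it points to the right repair. It does not remove the conflict, because the Objectives wording is a stated rule that an analyst could follow.

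Several stronger readings are tempting but not supported.

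- **That both target outcomes are contradictory.** Outcome 2 is worded the same way in the Objectives and Outcomes sections. It shares the ceiling only if baseline is part of the study period over which control is judged. That is a natural reading, but the text does not define it.
- **That two of the five secondary outcomes duplicate each other.** This is true of the Objectives list only.
- **That the outcome barely responds to treatment, or that success would be 0%.** Patients controlled at entry are eligible and are managed too, with titration in both directions, so the effect is diluted rather than removed. The 0% case needs every entrant to be above target. The Discussion speaks of uncontrolled blood pressure, but the eligibility criteria do not require it.
- **That the definition will be picked after results are seen.** A full protocol or analysis plan may already fix it; neither is shown.

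**Conclusion.** The point holds for outcome 1. Two incompatible definitions are in print, and the power statement and the analysis do not say which they use. On the Objectives wording the success proportion is capped at the share at target at entry, so the planned rates would need at least 70% of the intervention arm controlled at entry. This rests on reading the 20% as absolute and on taking the Objectives text literally. The end-of-study definition in Outcomes has no such ceiling. The size of the dilution depends on the baseline control share, which is not in the documents, so the figures in step 4 are a range and not an estimate.

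Outcome 2 needs a clarification rather than a correction. The primary outcome, its model and its sample size are untouched. The change should be made, but the trial's main conclusion does not depend on it. A reader might take the 0.60 to 0.70 power in step 3 as part of this point; it is a separate issue and does not add to its weight.

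**What to change.** Use one wording in Study Objectives, Outcomes, Sample Size Estimation and the analysis plan.

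- **Outcome 1:** mean home SBP below the protocol's own 130 mmHg threshold on the 12-month 7-day series, in all randomised patients. Drop the reference to baseline, and name this outcome in the power statement and in the Poisson model.
- **Outcome 2:** state that baseline is not counted, and list the post-baseline series on which it is judged, the same for both arms. The 6- and 12-month series are one option, since the primary model and the imputation already use them. Naming the series matters because the monthly-then-quarterly schedule depends on when a patient reaches target, so patients will have different numbers of series.

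Adjusting outcome 1 for baseline SBP is optional and not needed to resolve the conflict. The cost is wording in four sections; no new data or visits are needed. The 80% power claim should be rechecked separately once the outcome is named.

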**Figure 4. fig4-20543581221077500:**
[figure not shown]
Case manager protocol for BP lowering medications. *Note.* A home BP series will consist of a 24-reading average (duplicates measured in the morning and evening) taken over a consecutive 7-day period. Medications will be added in a guideline-concordant manner. We will ensure that all patients are at least on an Angiotensin converting enzyme-inhibitor (ACE-i) and diuretic, unless medically contraindicated. BP = blood pressure.

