### Study Procedures and Data Collection

At baseline, relevant demographic and health behavior information including age, sex, race, smoking, alcohol intake and details of patient’s medical history such as significant CV disease (eg, coronary artery disease, stroke, peripheral arterial disease, heart failure) and medication history (BP-lowering drugs—name, type, dosage, frequency, and duration) will be collected. Relevant clinical details such as body mass index (BMI) will also be recorded. Blood pressures will be measured and recorded following guideline recommendations.^10,11^ Other information that will be collected includes health care use in the past year (physician and/or emergency room visits, and hospitalizations) ascertained through patient self-reports and/or provincial administrative data sources, quality of life (Kidney Disease Quality of Life-36 [KDQOL-36]) and utility measurements (European Quality of life Five Dimension [EQ-5D]); and satisfaction with receiving health care, using the Patient Assessment of Care for Chronic Conditions (PACIC-2.0).^29-32^

Laboratory measurements will be carried out at baseline including serum electrolytes, serum creatinine (and estimated glomerular filtration rate), glycated hemoglobin (HbA1c), and urinary albumin/creatinine ratio (UACR). These measurements will also be taken at 6-months and 1 year.

Assessment of usability and acceptability is critical for all technology-enhanced care interventions to minimize risk of undesired consequences commonly seen post-implementation.^33,34^ End-user input into system design and operation is important throughout the evaluation process to reduce the risk that interventions will be ineffective, unusable, or unsafe. Usability testing will involve assessment of human-computer interaction—specifically, issues related to use, interface, design, function and will also include acceptability of the model of care for the caregivers. We will take a qualitative approach to this process by using focus groups. We plan to recruit 2 focus groups, 1 for patients in the telemonitoring arm and 1 for care providers (case managers and PCPs), with a target sample size of 5 to 8 participants in each group. The first 5 users typically identify 70% of severe usability problems and the first 8 users typically identify 85%; a higher sample size has low incremental yield due to data saturation.^
35

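### The only stated safety outcome from the repeated kidney and electrolyte tests is the proportion crossing fixed cut-offs, which is insensitive to moderate shifts at about 58 analysed patients per arm

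*Protocol article*

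**What the plan says.** All references are to the protocol article.

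- **Measurement.** Study Procedures and Data Collection lists serum electrolytes, creatinine with eGFR, HbA1c and UACR at baseline, then adds "These measurements will also be taken at 6-months and 1 year". Nothing restricts this to one arm. Potassium is not named there. I take it to be among the electrolytes, because the hyperkalaemia criterion needs it.
- **Outcome.** Study Objectives, secondary aim 5, compares the proportion of adverse events by arm. The kidney and laboratory examples are "worsening of kidney function (2x serum creatinine or 50% decline in estimated glomerular filtration rate [eGFR]), and/or electrolyte abnormalities [hyperkalemia ≥ 6.5 mmol/L". Adverse Events and Safety Monitoring repeats the same cut-offs. Outcomes lists adverse events and no continuous kidney or potassium measure.
- **Analysis.** Plan for Data and Statistical Analysis states: "For the dichotomous outcomes (patients who maintained the SBP guideline and adverse outcomes), we will use Poisson regression with robust error variance". The mixed model in that section is written for SBP. The linear regression is for continuous outcomes that are not measured repeatedly. eGFR appears otherwise as an adjustment covariate and a subgroup factor.
- **Why the laboratory values matter here.** The note to Figure 4 says of the case manager's protocol: "We will ensure that all patients are at least on an Angiotensin converting enzyme-inhibitor (ACE-i) and diuretic, unless medically contraindicated".

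**The concern.** The article treats worsening kidney function and electrolyte disturbance as possible harms of the intervention. The Introduction says that safety in this population is unknown, and the Discussion expects less over-treatment, with worsening renal function as one example. The measurements that could inform this will exist three times per patient.

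The stated outcome reduces each series to whether a cut-off was crossed. A shift in the mean that moves few patients across the cut-off leaves almost no trace in that outcome. The Introduction itself cites a kidney effect of telemonitoring on the continuous scale: "significant improvement in estimated glomerular filtration rate (5.35 mL/min/1.73 m^2^; [2.49, 8.21]; *P* < 0.001". At stake is whether the trial could recognise a moderate between-arm difference in kidney function or potassium from data that it already plans to collect.

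**Working it through.** **1. The plan's own sample size.** Sample Size Estimation aims at a "clinically important absolute difference in mean SBP of 10 mmHg between the intervention arm and the control arm", "Using a 2-sample t-test, alpha of 0.05 and power of 0.80, and assuming a common standard deviation of 19 mmHg". Taking the test as two-sided, the t-based solution for 10/19 is 57.6, so 58 per arm, and 58/0.80 = 72.5, so 73 recruited. Both stated figures reproduce. The section gives no event rate or power for the safety outcomes. I use n = 58 per arm and two-sided alpha 0.05 below.

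**2. Inputs that are assumptions.** The document gives no baseline eGFR distribution, laboratory SD or harmful shift. I assume:

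- eGFR: control mean change -1; intervention mean change -1 - 5.35 = -6.35; SD of change 8, 10 or 12; one common baseline value B, varied from 25 to 50. The size 5.35 is borrowed from the Introduction only for scale.
- Potassium: means 4.6 and 4.9 mmol/L (a shift of 0.3); SD 0.4, 0.5 or 0.6.

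**3. Halved-eGFR event.** With normal changes, P(event) = Φ((-B/2 - mean change)/SD). For B = 40 and SD 10, control is Φ((-20 + 1)/10) = Φ(-1.90) = 2.9%, and intervention is Φ((-20 + 6.35)/10) = Φ(-1.365) = 8.6%. Power is exact for Fisher's test.

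| Baseline eGFR | Event rate, control (SD 8 to 12) | Event rate, intervention (SD 8 to 12) | Power |
|---|---|---|---|
| 50 | 0.1-2.3% | 1.0-6.0% | 0-4% |
| 40 | 0.9-5.7% | 4.4-12.8% | 3-16% |
| 30 | 4.0-12.2% | 14.0-23.5% | 27-33% |
| 25 | 7.5-16.9% | 22.1-30.4% | 33-51% |

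Fisher's test is somewhat conservative compared with the planned Poisson model. As a cross-check on other assumed rates, 2% v 6% gives 5% power by Fisher and 19% by the normal approximation; 5% v 15% gives 31% and 43%. The picture is the same.

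**4. Mean change in eGFR, same patients.** Two-sample t-test with d = 5.35/SD: power is 95% (SD 8), 82% (SD 10) and 66% (SD 12), whatever the baseline.

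**5. Potassium.** Expected events per arm = 58 × [1 - Φ((6.5 - mean)/SD)]. At the largest SD, 0.6, control is 58 × 0.00077 = 0.04 and intervention is 58 × 0.00383 = 0.22. At SD 0.4 both are below 0.002. The mean comparison (d = 0.3/SD) has power 98%, 89% and 76% for SD 0.4, 0.5 and 0.6.

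**6. What the event comparison can show.** At 58 per arm, Fisher p < 0.05 needs at least 6 events v 0 (p = 0.027) or 8 v 1 (p = 0.032). With no events in 58 patients, the one-sided 95% upper limit for the true rate is 1 - 0.05^(1/58) = 5.0%.

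**The case against.** The strongest reply is that this is a condensed article. The adverse events in secondary aim 5 are introduced as examples, the full protocol and SAP are not shown, and laboratory summaries are often placed there. The SAP may well add them. What stands against this is that the article does fix the scale: aim 5 is a proportion, and adverse outcomes are assigned to a dichotomous analysis. Neither of its continuous-outcome methods fits eGFR or potassium measured at both 6 and 12 months, because one is for outcomes without repetition and the other is written for SBP.

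A reader might infer that a real harm would be reported as no difference, or that there would be almost no events. The documents do not support either. Effect sizes are to be reported with 95% confidence intervals, so sparse events would show as imprecision. Nowhere does the article say that absence of events means safety. A large excess would still be visible, and eligibility reaches down to just above eGFR 15, where halving needs a smaller fall. Even at baseline 40 with SD 12, the assumed model expects 58 × 5.67% = 3.3 v 58 × 12.77% = 7.4 events. The appeal to confidence intervals has a limit, however: if one arm has no events, the Poisson model gives no finite ratio.

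The figure 5.35 is also open to challenge. It is a pooled benefit of telemonitoring, whereas both arms here receive telemonitoring, and I reverse its sign. It is not the plan's effect size for this contrast. Finally, low power for adverse events is normal in a trial sized on SBP, the article claims none for safety, and an independent committee reviews cases. That is fair, but it does not explain leaving a more sensitive comparison of existing data unstated.

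**Conclusion.** The point holds as one of sensitivity. The stated laboratory safety outcome would probably miss a moderate kidney or potassium harm at the planned size, while a comparison of means on the same data would have a reasonable chance of finding it. For eGFR the contrast is 0-51% against 66-95% power across assumed baselines of 25 to 50 and SDs of 8 to 12. For potassium it is fewer than one expected event per arm against 76-98% power.

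The direction held across every assumption tried; the size did not. It depends most on baseline eGFR, and it rests on a common baseline value, normal changes and shifts that the document does not specify. The finding concerns the scale of analysis only. It says nothing about whether the cut-offs are clinically right, and it does not show that the trial would declare the intervention safe.

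**What to change.** 1. In Study Objectives (aim 5) and Outcomes, add as safety outcomes the between-arm differences in eGFR and in serum potassium at 6 and 12 months.
2. In Plan for Data and Statistical Analysis, state that each is estimated by the mixed model already described (time point, intervention, their interaction, random participant effect), with the outcome's own baseline value as covariate, and reported with a 95% confidence interval.
3. Keep the existing event definitions unchanged and report them as counts by arm.
4. State that few or no threshold events will not, on their own, be read as evidence of no kidney or electrolyte harm.

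The cost is two extra models on data already collected, a paragraph of text, and a few more safety comparisons without multiplicity adjustment. These comparisons would also be weak for small shifts: 27-52% power for 3 mL/min/1.73 m² (d = 3/SD, SD 12 to 8) and 14-27% for 0.1 mmol/L (d = 0.1/SD, SD 0.6 to 0.4). The intervals should therefore carry the interpretation. No clinical threshold or management rule changes.
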